### **Clinical laboratory parameters**

Hematological (CBC) and biochemical (ALT, creatinine) laboratory parameters will be measured at specific time points, Days 0, 7, 30, 37, 60, 67 and 90. Clinically relevant abnormal values based on reference intervals determined in rural Malian children will be tabulated and a trend analysis could be performed if deemed necessary. Laboratory abnormalities will be graded on a scale of 1-4 as defined in relevant SOPs.

### **12.5.4 Analysis of CMI responses**

Correlation will be measured 1) between serum anti-AMA-1 antibody levels and T-helper cell responses; and 2) between avidity and/or classes and IgG sub-classes of anti-AMA-1 antibodies and T-helper cell responses. Correlations between continuous measures of immune response will be assessed using the standard Pearson as well as Spearman rank correlation coefficients, on  $\log_{10}$  transformed data when a logarithmic transformation results in a distribution more nearly normal than the distribution of untransformed values. Association between a continuous and a categorical measure will be assessed using t-tests or analysis of variance, or the analogous tests on ranks. Association between categorical measures will be assessed using chi-square or exact tests. Appropriate summary descriptive statistics (e.g., means and standard deviations or medians and ranges) will be presented. Effects of covariates (e.g., gender, ethnicity) will be assessed using regression models.

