| Objectives:                           | 
Primary:
 

• Evaluate the safety and reactogenicity of FMP2.1/AS02A in children naturally exposed to P. falciparum malaria infection

 
Secondary:
 

• To measure the magnitude and duration of antibody response to FMP2.1 by ELISA

                                                                                                                                                                                                                                                         |
| Description of Study Design:          | Randomized, controlled dose-escalation Phase 1 trial of the FMP2.1/AS02A malaria vaccine, using rabies vaccine as a control. Children aged 1-6 years will be randomized to three groups. Twenty subjects will be enrolled in cohort 1 and 40 subjects each in cohorts 2 and 3. Children within each cohort will be randomized in a 3:1 ratio to receive 10, 25 or 50 µg of FMP2.1 (in cohorts 1, 2 and 3, respectively) adjuvanted with a proportionate volume of the AS02A, or rabies vaccine. Thus a total of 75 children will receive the malaria vaccine and 25 the rabies vaccine. Immunizations will |

be given on days 0, 30 and 60 in a staggered fashion, with the first administrations of the 25 and 50 µg dose levels of FMP2.1 following the first administration of the 10 and 25 µg dose levels, respectively, by 2-3 weeks. Solicited adverse events will be recorded on the days of immunization and days 1, 2, 3 and 7 after each immunization, and unsolicited adverse events will be recorded for 30 days after each immunization. Children will be followed for one year after the last immunization. Sera will be collected for anti-FMP2.1 antibody titers on the days of immunization and 14 days after each immunization as well as three, six, nine and twelve months after the first immunization.

**Estimated Time to Complete Enrollment:** 45 days

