#### 2.4.4.2 Immunogenicity Data

**Humoral Immune Response:** Volunteers receiving either the 25 or 50 µg dose of FMP2.1 developed anti-FMP2.1 antibody responses that were significantly higher than the rabies vaccinated volunteers. Two weeks after the third immunization there were 6- and 11- fold increases in anti-FMP2.1 titers respectively in the 25 and 50 µg dosage groups over the rabies control group. After the second immunization there was a significant difference between the geometric mean titers of the FMP2.1 vaccinated individuals and the rabies vaccinated individuals achieved significant difference ( $p < 0.05$  on log-transformed data). However, there was no significant difference between the 25 and 50 µg dosage groups after the second immunization but there is a trend towards significance ( $p = 0.07$ ) (Table 8). Similarly to the malaria-naïve volunteers immunized in Malaria-033, the coefficients of variance for the log transformed data from the malaria-exposed volunteers immunized in Malaria-037 were 10.1% or less after the second immunization whereas in the rabies

vaccinated individuals the average coefficient of variance was 20.9% and did not vary significantly over time (Figure 3). The baseline antibody titers were higher in this malaria-exposed population than in the malaria-naïve participants in Malaria-033, but the magnitude of the post-immunization responses was similar.

**Table 8 Anti-FMP2.1 Geometric Mean Antibody Titers by ELISA  
(Malaria-037 [Malaria-Exposed Adults])**

|                                   | Day
0  | Day
14 | Day
30  | Day
44 | Day
60  | Day
74 | Day
90 | Day
180 |
|-----------------------------------|-----------------------|-----------|------------------------|-----------|------------------------|-----------|-----------|------------|
| ~25 µg FMP2.1 in
0.25 mL AS02A |                       | 30794     | 31805                  | 55246     | 61439                  | 89857     | 60967     | 50750      |
| ~50 µg FMP2.1 in
0.5 mL AS02A  | 23500                 | 69752     | 55086                  | 100590    | 119191                 | 150738    | 102813    | pending    |
| Rabies vaccine
(RabAvert®)     | 14355                 | 13857     | 12691                  | 13941     | 16030                  | 14064     | 10425     | 7846       |

 Immunizations were given on days 0, 30, and 60.

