#### **9.3.5 CMI and antibody avidity assays**

PBMCs will be cryopreserved and transported to the University of Maryland for CMI assays. The objectives of CMI and secondary serological studies are twofold: (1) Accurately measure humoral immunity by quantifying antibody responses to the antigen AMA-1 and (2) Systematically analyze T-cell responses to both full-length recombinant AMA-1 (rAMA-1) antigen and to synthesized peptides derived from domain I of the AMA-1 ectodomain. Based on these results, we will address three important questions: (1) Is the level of anti-AMA-1 antibody levels in serum (as measured in end-point dilutions by ELISA) correlated with T-helper cell responses? (2) What are the characteristics of memory T cell responses? And (3) are the avidity and/or classes and IgG sub-classes of anti-AMA-1 antibodies correlated with memory and effector T-helper cell responses?

In addition to antibody levels as measured by ELISA titers, avidity of antibodies may be important measures of a protective immune response. Antibody avidity and affinity assays will be performed at the University of Maryland to test the hypothesis that the avidity of antibodies to AMA-1 correlates with allele-specific T-helper cell responses to AMA-1.

A list of assays follows. Results of these studies will not be used as measures of immunogenicity for purposes of choosing a dose for further clinical development. Methods for some of these assays are currently being developed and refined. As noted above, these assays will be prioritized by the investigators to ensure optimal use of limited sera and cells.

- Antibody avidity studies
- Identification of immunodominant T cell epitopes involved in class I (e.g., CTL) and II (e.g., Th1, Th2) MHC restricted T cell responses
- Measurement of cytokine-producing cells to soluble antigens by ELISPOT
- Cytokine measurements using optimized Cytometric Bead Array (CBA) technology
- Measurement of memory T cell subpopulations
- Measurement of memory B cell pools
- Lymphoproliferative responses to AMA-1

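### Section 12.5.4 correlates antibody with T-helper response without conditioning on vaccine group, so a coefficient that includes controls partly measures treatment assignment

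*Protocol*

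**What the plan says.** Section 9.3.5 asks, as its first question, "Is the level of anti-AMA-1 antibody levels in serum (as measured in end-point dilutions by ELISA) correlated with T-helper cell responses". Its third question asks the same of avidity, antibody classes and IgG subclasses. It also states a hypothesis that avidity correlates with allele-specific T-helper responses. Its second question, on the character of memory T-cell responses, is not a correlation.

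Section 12.5.4 sets the analysis: "Correlation will be measured 1) between serum anti-AMA-1 antibody levels and T-helper cell responses", followed by the avidity and subclass counterpart. The method is fixed: "Correlations between continuous measures of immune response will be assessed using the standard Pearson as well as Spearman rank correlation coefficients", with a log10 transformation where that brings the data closer to normal. The only adjustment is a separate sentence: "Effects of covariates (e.g., gender, ethnicity) will be assessed using regression models". Vaccine group, dose and visit are not mentioned.

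Neighbouring sections do give a grouping. Section 12.5.2 presents antibody results by vaccine group and time point, and section 12.5.3 tabulates safety by group and administration.

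The Protocol Summary gives the mix of treatments: "Thus a total of 75 children will receive the malaria vaccine and 25 the rabies vaccine". Sections 9.2.2 and 9.2.3 describe both the antibody and the cellular responses from Day 90 onward as boosted by the vaccine.

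**The concern.** Section 9.3.5 concerns how the parts of the immune response go together: does a child with more, or more avid, antibody also have a stronger T-helper response? A correlation over vaccinees and controls together answers a different question. If vaccination raises both measures, vaccinees sit high on both and controls low on both. The scatter then slopes upward even if, within each arm, antibody says nothing about T-helper response. The coefficient partly re-detects that the vaccine is immunogenic on both assays. Ranks and log transformation do not remove this, because the shared cause is still in the data.

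At stake is the mechanistic conclusion. Section 9.3.4 says these additional studies may inform further development of AMA-1 vaccines, and an association produced by treatment assignment could be read as a link between the two arms of immunity.

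**Working it through.** **The plan's own figure.** The protocol gives no number for the correlation analysis. It does quantify the antibody effect in the Malian adult trial: "there were 6- and 11- fold increases in anti-FMP2.1 titers respectively in the 25 and 50 µg dosage groups" over the rabies group, two weeks after the third dose. Table 8, Day 74: 89,857 / 14,064 = 6.4 and 150,738 / 14,064 = 10.7. The figures reproduce.

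**Inputs.**
- Group sizes: 15, 30 and 30 vaccinees (10, 25, 50 µg) and 25 rabies (section 4.1).
- Day 90 GMTs, Table 8: 60,967 (25 µg), 102,813 (50 µg), 10,425 (rabies). In log10: 4.785, 5.012, 4.018. The 10 µg dose was not tested in that trial; it is set equal to 25 µg (assumption).
- Spread of log titre (section 2.4.4.2): coefficients of variation in "malaria-exposed volunteers immunized in Malaria-037 were 10.1% or less after the second immunization"; for controls, "vaccinated individuals the average coefficient of variance was 20.9" per cent. SD = CV × mean log10: 0.101 × 4.785 = 0.483; 0.101 × 5.012 = 0.506; 0.209 × 4.018 = 0.840.
- T-cell measure: SD 1 in every arm, independent of antibody within arm, shifted by *d* SD in all vaccinees. The documents give no *d*, so it is ranged.
- All 100 children have both results at one visit; two-sided 5% level (assumptions).

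**Closed form.** With control fraction q = 0.25, q(1 − q) = 0.1875.
- Vaccinee mean antibody: (45 × 4.785 + 30 × 5.012) / 75 = 4.876. Difference from controls: 4.876 − 4.018 = 0.858.
- Within-arm variance: 0.45 × 0.483² + 0.30 × 0.506² + 0.25 × 0.840² = 0.358.
- Between-arm variance about the overall mean 4.661: 0.45 × 0.124² + 0.30 × 0.351² + 0.25 × 0.643² = 0.147.
- Total 0.505; SD 0.711.
- Expected pooled r = 0.1875 × 0.858 × d / [0.711 × √(1 + 0.1875 d²)].

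At d = 0.5: 0.0804 / (0.711 × 1.023) = 0.11. At d = 1: 0.161 / (0.711 × 1.090) = 0.21. By Fisher's z with N = 100, the chance of significance at d = 1 is Φ(atanh(0.208) × √97 − 1.96) = Φ(0.12), about 55%.

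**Simulation** (10,000 trials per row, zero within-arm association; repeat runs differ by about one percentage point):

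| T-cell shift (SD) | Pearson, pooled | Spearman, pooled | Conditioned on group |
|---|---|---|---|
| 0 | 5% | 5% | 5% |
| 0.25 | 9% | 8% | 5% |
| 0.5 | 20% | 16% | 5% |
| 1 | 56% | 45% | 5% |
| 1.5 | 83% | 71% | 5% |

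The mean pooled Pearson r at 1 SD was 0.21, as in the closed form. Over all scenarios, including those below, the conditioned tests rejected in 4.6% to 5.8%.

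**Sensitivity to the antibody separation** (equal SDs in all arms; Pearson/Spearman):
- 1 SD apart: about 13%/13% at a T-cell shift of 0.5 SD and 35%/32% at 1 SD.
- 2 SD apart: about 29%/26% and 76%/71%.
- 3 SD apart: about 39%/32% and 92%/83%.

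**Where the problem is absent.** With no arm difference on either measure, as at Day 0, the pooled tests reject in 5%. Among the 75 vaccinees alone they reject in 5%, or up to 6% if the T-cell shift is graded by dose.

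**The case against.** The strongest reply is that pooling is inferred from silence. Section 12.5.4 names coefficients, not a population or visit, and section 12.5 leaves a final analysis plan to be agreed before database lock. That is fair, and a reader should not infer that the protocol says the arms are combined. But the coefficient itself is fixed, and a later plan that followed the section literally would carry the problem forward.

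The covariate list is open, so it would be too strong to say that vaccine group is excluded. Still, the dominant shared cause is unnamed, and a separate regression of covariate effects does not turn a standard coefficient into a partial one.

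It can also be argued that section 9.3.5 asks only whether the measures are correlated, without saying within arm, and that section 12.5.4 speaks of measuring correlation, with no test or alpha for these coefficients. Both are true. A pooled coefficient is a correct description of the mixed sample; the error lies in taking it, or its p-value, as evidence of an association between individuals' responses.

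Three other inferences are tempting but unsupported:
- That repeated samples from a child would be treated as independent. Nothing says so, and section 12.2 lists cellular responses at each time point, which points to visit-by-visit analysis.
- That all three questions in section 9.3.5 are affected. Only the first and third are correlations.
- That dose choice is at risk. Section 9.3.5 bars these results from dose selection, and sections 3.1.3 and 3.2.2 name only ELISA antibody.

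**Conclusion.** The concern holds in a limited form. Taken at its plain reading, with controls included at a post-vaccination visit, the specified coefficient partly reflects treatment assignment and would be called significant too often as evidence of an individual-level association. The excess runs from slight (8–9% at a 0.25 SD shift) to severe (70% or more at 1.5 SD). There is none if vaccination does not move the T-cell measure.

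The size rests on assumptions: the T-cell shift, adult antibody values applied to children aged 1–6, the 10 µg value, the 5% level and 100 complete pairs. Section 9.3.5 itself expects limited sera and cells, and fewer pairs would lower the rejection rates. The vaccinee CV is an upper bound, and a smaller one would raise them. Avidity was not simulated and no vaccine effect on it is documented; the same mechanism applies there only if vaccination shifts avidity as well.

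The consequence is confined to interpreting questions 1 and 3 and the avidity hypothesis in section 9.3.5. The primary safety objective and the choice of dose are untouched. The wording should be corrected because a better method is available at almost no cost.

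**What to change.** In section 12.5.4, state that the correlations are estimated at a named post-vaccination visit (Day 90, the primary analysis point, is a natural choice), in one of two ways:
- within FMP2.1/AS02A recipients only; or
- in all children as partial Pearson and partial Spearman correlations adjusted for vaccine group (10, 25, 50 µg or rabies).

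Report the pooled unadjusted coefficient, if wanted, as descriptive only.

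No sample, assay or visit changes. With 100 pairs, adjusting for four groups takes the residual degrees of freedom from 98 to 95. Restricting to vaccinees leaves at most 75 pairs. The coefficient will usually be smaller, because the part due to treatment assignment is removed.

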### 2.3.1 The AMA-1 antigen

Another promising antigen for blood-stage vaccine development is the apical membrane antigen 1 (AMA-1), a surface protein expressed during the asexual blood stage of *P. falciparum*. AMA-1 is produced as an 83-kDa polypeptide by mature schizonts in infected erythrocytes (12), and localizes in the microneme, an apical secretory organelle of the merozoite containing ligands for binding red cell receptors (13). The protein is processed to a 66-kDa protein that is subsequently exported to the merozoite surface where it plays a critical role in invading erythrocytes (14-17).

*P. falciparum* AMA-1 consists of a signal sequence, a large extracellular domain (ectodomain of 546 amino acids), a transmembrane domain (21 amino acids), and a C-terminal cytoplasmic domain (55 amino acids) (18). Comparisons between all of the known amino acid sequences of AMA-1 homologues indicate greater than 50% sequence identity, with 16 cysteine residues conserved in all sequences (19-21). All of the cysteines are found in the ectodomain of the molecule, which is stabilized by eight intramolecular disulfide bonds (22).

Seroepidemiologic studies conducted in West Africa and western Kenya demonstrate that natural antibody responses to AMA-1 are widespread and highly prevalent (23). Serological and cellular immune responses to AMA-1 increase with age in populations subject to continued exposure to malaria infection (24). Preliminary studies in Donéguébougou, Mali, demonstrate that natural antibodies exist in a large proportion of individuals (>90%) in this area of intense, seasonal transmission. In a cross-sectional study of 200 individuals aged 6 months to 45 years conducted in 2002 and 2003, median anti-AMA-1 antibody titers reached approximately 1000 at the peak of malaria transmission, although significant variation was seen between different age groups (25).

The naturally acquired antibodies to AMA-1 found in people living in malaria-endemic areas inhibit the growth of *P. falciparum* *in vitro* (26). This inhibition was dose-dependent and anti-AMA-1 antibodies recognized both strain-specific and conserved epitopes. From this evidence, it is reasonable to postulate that boosting the natural antibody response to AMA-1 through vaccination may protect an individual from illness due to the asexual blood stage of *P. falciparum* infection.

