## **5.4 Treatment Assignment Procedures**

### **5.4.1 Randomization Procedures**

Individual participants will be randomized to receive one of three escalating doses of FMP2.1/AS02A, or rabies vaccine. One hundred participants will be assigned to Cohort 1 (n=20), Cohort 2 (n=40) or Cohort 3 (n=40) in the order they are enrolled with stratification for age by two-year increments (1-2 years, 3-4 years, 5-6 years) but without stratification for gender, and randomized within cohorts to receive FMP2.1/AS02A or rabies vaccine. Because cohort sizes are not divisible by three, the numbers in each stratum may be either 6 or 7 in each age stratum for Cohort 1 and either 13 or 14 in Cohorts 2 and 3. Cohort 1 will be randomized in a 3:1 ratio to receive 10µg of FMP2.1 adjuvanted with 0.1 mL of AS02A (n=15) or rabies vaccine (n=5). Cohort 2 will be randomized in a 3:1 ratio to receive 25µg of FMP2.1 adjuvanted with 0.25 mL of AS02A

(n=30) or rabies vaccine (n=10). Cohort 3 will be randomized in a 3:1 ratio to receive 50µg of FMP2.1 adjuvanted with 0.50 mL of AS02A (n=30) or rabies vaccine (n=10). The total sample size for the rabies group will thus be 25.

Within each cohort, treatments will be assigned to participant ID numbers in randomized blocks of a size that will not be stated in this protocol to avoid compromising masking, per DMID guidelines. Randomization to either of the two vaccines will be done using a computer-generated randomization list. The randomization list will contain sequential codes linking a participant ID number to a vaccine assignment. Participant ID numbers will be assigned to participants of each cohort in the order in which they are enrolled in the trial.

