### **12.5.1 Analysis of demographics**

Demographic characteristics (age, sex, and place of residence) of each study cohort will be tabulated. The mean age (plus range and standard deviation) by sex of the enrolled participants, as a whole and per group will be tabulated.

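### Section 12.5.4 correlates antibody with T-helper responses without adjusting for age, although the protocol says both rise with age

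*Protocol*

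**What the plan says.** Protocol section 12.5.4 sets the target of the cell-mediated immunity (CMI) analysis: "Correlation will be measured 1) between serum anti-AMA-1 antibody levels and T-helper cell responses", and likewise between T-helper responses and antibody avidity, class and IgG subclass. It fixes the method: "Correlations between continuous measures of immune response will be assessed using the standard Pearson as well as Spearman rank correlation coefficients", after a log transformation where that helps. No partial or age-stratified coefficient is named. A separate closing sentence adds: "Effects of covariates (e.g., gender, ethnicity) will be assessed using regression models".

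Three other places bear on this:

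- Section 2.3.1 states: "Serological and cellular immune responses to AMA-1 increase with age in populations subject to continued exposure to malaria infection". For antibody titers in a Malian sample aged 6 months to 45 years, it adds that "significant variation was seen between different age groups".
- Section 5.4.1 assigns children to cohorts "with stratification for age by two-year increments (1-2 years, 3-4 years, 5-6 years) but without stratification for gender".
- Sections 9.2.2 and 9.2.3 schedule both serum and PBMC samples on Day 0, so a pre-vaccination correlation can be computed.

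Section 12.2 lists cellular responses among the secondary endpoints. Section 9.3.5 states that the CMI and avidity results will not be used to choose a dose.

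**The concern.** The two variables to be correlated are the two that the protocol itself says move with age in exposed populations. Each cohort spans all three age bands by design, so age varies within every arm. Older children have had more exposure, and that can raise both measures whether or not antibody and T-helper responses are linked in children of the same age. A crude coefficient cannot separate the two explanations.

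Age is also the factor that the design treats as important, while gender is expressly not stratified. The illustrative covariates nonetheless name gender and not age. The regression sentence speaks of assessing covariate effects, not of adjusting the correlations. Adding age to its examples would therefore not by itself change the Pearson and Spearman results.

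At stake is how questions 1 and 3 of section 9.3.5 are read, namely whether antibody level, avidity or subclass tracks T-helper response. A positive answer from crude coefficients could reflect shared age and exposure.

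**Working it through.** The protocol states no figure for this analysis, so there is none to reproduce. The check asks how large an artefact a shared age effect could produce.

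**Inputs from the protocol.** Arm sizes are 15 (10 µg), 30 (25 µg), 30 (50 µg) and 25 (rabies). That gives 15 + 30 + 30 = 75 on malaria vaccine and 75 + 25 = 100 in all. Ages are 1–6 years.

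**Assumptions, not in the protocol.**

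- Each measure correlates linearly with age at r = 0.2, 0.3 or 0.5.
- Antibody and T-helper response are independent at a given age.
- The test is two-sided at 5%. Section 12.5.4 sets no level for these correlations.

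**Step 1: induced correlation.** With independence given age, the crude correlation is the product of the two age correlations, ρ = r × r:

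- 0.2 × 0.2 = 0.04
- 0.3 × 0.3 = 0.09
- 0.5 × 0.5 = 0.25

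**Step 2: chance of a significant crude correlation.** By the Fisher z approximation, d = atanh(ρ) × √(n − 3), and the rejection probability is Φ(d − 1.96) + Φ(−d − 1.96).

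Worked case, ρ = 0.25 and n = 30: atanh(0.25) = 0.2554 and √27 = 5.196, so d = 1.327. The probability is Φ(−0.633) + Φ(−3.287) = 0.264.

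All cases:

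| r with age | induced ρ | n = 15 | n = 25 | n = 30 | n = 75 | n = 100 |
|---|---|---|---|---|---|---|
| 0.2 | 0.04 | 5.2% | 5.4% | 5.5% | 6.3% | 6.8% |
| 0.3 | 0.09 | 6.1% | 7.1% | 7.6% | 11.9% | 14.4% |
| 0.5 | 0.25 | 14.3% | 22.4% | 26.4% | 58.2% | 71.1% |

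**Step 3: check by simulation.** This used 10,000 trials per setting, with age uniform from 1 to 7 years (that is, up to the seventh birthday). Crude Pearson rejection was 5.9%, 7.8% and 26.3% at n = 30, and 6.6%, 14.7% and 72.0% at n = 100, for r = 0.2, 0.3 and 0.5. These agree with the table to within one percentage point.

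**Step 4: effect of adjusting.** The partial correlation given age is (r_AT − r_A·r_T) / √[(1 − r_A²)(1 − r_T²)]. Here r_AT is the crude antibody–T-helper correlation, and r_A and r_T are their correlations with age. When r_AT = r_A·r_T it is zero. In the same simulations its mean was about 0 and its rejection rate was 4.8% to 5.3% at n = 30, 75 and 100 for every age effect in the table. Under a linear age effect, adjustment removes the artefact.

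**The case against.** The strongest reply is that the covariates are given as examples. A reader might infer that age has been left out of the models, but the text does not say so. Section 12.5 provides for a final analysis plan before database lock, and a full covariate list can properly sit there. That stands. It does not reach the correlations themselves, because section 12.5.4 names the coefficients and they are crude.

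A reader might also infer that age will by itself produce a positive finding. The documents do not support this. Section 2.3.1 gives a direction and no size, and its Malian sample runs to age 45, so the gradient within ages 1–6 is unknown. Even at r = 0.5, about 74% of arms of 30 would show nothing significant. Nor can one age correlation be carried safely from baseline to vaccinated arms. Section 2.4.4.2 reports that, in Malian adults after the second immunization, the coefficient of variation of log titer was 10.1% or less in vaccinees, against an average of 20.9% in rabies controls. Those data say nothing directly about age, but they show that vaccination changes the titer distribution.

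The largest figures are for 100 children pooled at Day 0, where no one would credit the vaccine with the association. That is fair. The problem there is taking shared exposure for a link between humoral and cellular responses.

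Section 9.3.5 asks only whether the measures are correlated, and a crude coefficient answers that literally. This is a reason to keep the crude coefficients beside the adjusted ones.

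Finally, a reader might infer that ethnicity is named as a covariate but never recorded, since section 12.5.1 says only that "Demographic characteristics (age, sex, and place of residence) of each study cohort will be tabulated". That sentence lists what is tabulated, not everything collected. The case report forms are not shown, so the inference is not supported.

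**Conclusion.** The point holds as a minor one. Section 12.5.4 commits to crude antibody–T-helper correlations and does not name age, while section 2.3.1 says that both sides of the correlation rise with age and section 5.4.1 makes age the stratification factor. Shared age and exposure can create or inflate the association. The risk is clearest at Day 0 and in the rabies group, where responses reflect natural exposure, and when children are pooled, where the larger sample makes a small induced correlation easier to detect.

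The size depends on age correlations that the protocol does not give. At 0.2 to 0.3 the effect within one arm of 30 is negligible. At 0.5 it is material, at about five times the nominal error rate in an arm of 30 (26.4 / 5 ≈ 5.3) and about fourteen times with 100 children (71.1 / 5 ≈ 14). These figures assume linear age effects, no link at a given age, and a 5% test.

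Nothing here touches the safety endpoints or the choice of dose.

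**What to change.** In section 12.5.4, or in the analysis plan that implements it:

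1. Report partial Pearson and partial Spearman correlations adjusted for age, as a continuous variable, beside the crude ones.
2. Include age in the CMI regression models.
3. Base any statement that humoral and cellular responses are linked on the adjusted coefficients, and keep the crude ones as description.

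The cost is one degree of freedom per correlation and a little extra analysis. Age is already an eligibility criterion, a stratification factor and a tabulated variable, so no new data are needed.
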